Aims 3 & 4: Due to potential non-independence of FSWs within CBOs, mixed linear models will be used to determine if participation in the *Mujer Segura* intervention was effective in improving sexual behavior outcomes (e.g., condom use, ratio of unprotected to protected sex) compared to the treatment-as-usual condition. Within this model, intervention condition, time, and the intervention-by-time interaction will be entered as our primary independent variables. Because participants will be nested within CBOs, this factor will be entered as a random effect. A first-order autoregressive process (a stationary AR[1] process) will be used to characterize the autocorrelation structure.

Our second set of analyses will examine efficacy of the intervention for reducing incident HIV and other STIs. We will compare intervention groups in terms of cumulative incidence and incidence density. In both cases, the numerator will be the number of women who acquire the STI in question during follow-up; for cumulative incidence, the denominator will be the total number of at-risk women, whereas for incidence density the denominator will be the total number of person years for at-risk women. For each HIV/STI outcome, Poisson regression will be used to determine if group differences are statistically significant. As an indication of effect size, we will calculate the Number Needed to Treat (NNT) for each STI outcome, where NNT represents the number of participants in the intervention who would need to be treated before one fewer person contracted the STI than would be the case had all participants received the comparison condition. Aim 4 will be addressed by using FSW behavioral outcomes described above (aim 3).

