We evaluated statistical power to detect main effects and interaction effects in Hypotheses 3 and 4. Our power analyses reveal that we have an excellent chance of detecting significant main effects and interactions in our data. Hypothesis 3 uses a repeated measures design with two conditions. Assuming an attrition rate of 20%, which we achieved in *Mujer Segura*, we will have 384 subjects per group for a total of 768 subjects at the end of five years. We used findings from the parent project intervention with FSWs described in Preliminary Studies to estimate overall reductions in high-risk sex and incident STIs. We observed a 36% reduction in unprotected sex in the intervention (i.e., 18% vs. 36%), and a 40% decrease in overall STI incidence in the intervention group relative to the control (i.e., 20% vs. 38%). To estimate power in our sample, assuming a 36% reduction in unprotected sex at six-month follow-up, we calculated the following: N=384 per group, alpha = .05, and a 36% reduction in mean number of unprotected sex acts. If subjects in our experimental condition reduced the number of unprotected sex acts while the control condition did not change (i.e., group x time interaction), we would detect significant differences greater than 78% of the time. Power is slightly higher for STIs (i.e., .81). The addition of a covariate for fidelity to test hypothesis 4 does not substantially impact power estimates. Therefore, though our study is not designed to replicate findings from the parent project, we have sufficient power to detect differences between groups.

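### Poisson regression is the only test named for cumulative STI incidence, a yes/no outcome; with model-based errors it is conservative, by about 16% in the SE at 20% vs 38% and about 5% at lower risks

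*Protocol*

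**What the plan says.** Protocol section 8, Data Analysis and Interpretation, Aims 3 & 4, sets out two measures for incident HIV and STIs: "We will compare intervention groups in terms of cumulative incidence and incidence density". Both count the women who acquire the infection and differ only in the divisor. The text on the first measure reads "for cumulative incidence, the denominator will be the total number of at-risk women"; the second divides the same count by the follow-up time these women contribute, in person-years. One test follows: "For each HIV/STI outcome, Poisson regression will be used to determine if group differences are statistically significant". Neither a variance estimator nor a separate method for the binary measure is named. The same paragraph promises a number needed to treat (NNT) for each STI outcome.

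The power paragraph takes its STI planning rates from the parent trial, "a 40% decrease in overall STI incidence in the intervention group relative to the control (i.e., 20% vs. 38" percent, and expects that "we will have 384 subjects per group for a total of 768 subjects at the end of five years". It states STI power of .81. Section 7 reports the parent trial's incidence densities as 13.8 vs 24.92 per 100 person-years for STIs combined and 0 vs 2.01 for HIV.

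**The concern.** A proportion of women infected has variance p(1-p) per woman. Poisson regression with its default, model-based errors assumes variance p. The two nearly agree when p is small and diverge as p grows, and the protocol's planning risks of 20% and 38% are not small.

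The consequence is an overstated standard error: confidence intervals that are too wide and a test that rejects less often than its nominal level. Hypothesis 3 names STI incidence as an outcome, and section 12 counts lower HIV and STI incidence among the primary outcomes sought. Incidence density is not affected, because Poisson regression on person-time is a standard choice there.

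**Working it through.** **Inputs.** From section 8: 384 women per group and risks of 20% (intervention) and 38% (control). From section 7: the densities above. Calculations are two-sided at 5% and treat women as independent.

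**The plan's own figures.** 960/2 × 0.8 = 384 per group, which reproduces. The stated power of .81 does not: at 20% vs 38% with 384 per group, a two-proportion test has power above .999. Also, 1 - 20/38 = 47%, not 40%. So .81 cannot be used to infer which variance the sponsor had in mind.

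**Six-month risks implied by section 7.** Assuming a constant rate over half a year, 0.138 × 0.5 = 6.9% and 0.2492 × 0.5 = 12.46%. Using 1 - exp(-rate × 0.5) instead gives 6.67% and 11.72%.

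**Standard error of the log risk ratio, n per group.**
- Model-based Poisson: SE_P = sqrt[1/(n·p1) + 1/(n·p2)]
- Binomial or robust: SE_B = sqrt[(1-p1)/(n·p1) + (1-p2)/(n·p2)]
- Ratio: k = SE_P/SE_B

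| Risks | SE_P | SE_B | k |
|---|---|---|---|
| 20% vs 38% (as stated) | 0.1410 | 0.1211 | 1.164 |
| 22.8% vs 38% (literal 40% cut from 38%) | 0.1352 | 0.1143 | 1.183 |
| 20% vs 33.3% (literal 40% cut to 20%) | 0.1443 | 0.1250 | 1.155 |
| 6.9% vs 12.46% | 0.2422 | 0.2312 | 1.048 |
| 6.67% vs 11.72% | 0.2476 | 0.2368 | 1.045 |

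Fitting a Poisson model to 77/384 vs 146/384 gave 0.1408 with model-based errors and 0.1209 with robust errors, again a ratio of 1.164. For HIV, 2.01 per 100 person-years over six months is a risk of about 1%; at that risk k = 1/sqrt(0.99) = 1.005.

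**Type I error.** With the same risk p in both arms, k = 1/sqrt(1-p) and the true size is 2[1 - Φ(1.96k)].

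| Common risk | k | True size of a nominal 5% test |
|---|---|---|
| 5% | 1.026 | 4.4% |
| 10% | 1.054 | 3.9% |
| 20% | 1.118 | 2.8% |
| 29% (midpoint of 20% and 38%) | 1.187 | 2.0% |
| 38% | 1.270 | 1.3% |

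A simulation of 200,000 trials gave 2.8%, 2.0% and 1.3% at the last three risks. Robust errors gave 4.9% to 5.0%.

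**Power.** The estimate's true spread is SE_B and the Poisson test's threshold is 1.96k, so power = Φ(|log RR|/SE_B - 1.96k). Setting k = 1 gives the binomial test.
- 20% vs 38%: 0.6419/0.1211 = 5.30. Binomial: Φ(5.30 - 1.96) = .9996. Poisson: Φ(5.30 - 2.28) = .9987.
- 6.9% vs 12.46%: 0.5910/0.2312 = 2.56. Binomial: Φ(2.56 - 1.96) = .72. Poisson: Φ(2.56 - 2.05) = .69.
- Illustration only, 28.25% vs 38%, a difference chosen so that the binomial test has power .81: SE_B = 0.1042, k = 1.216, 0.2965/0.1042 = 2.84. Poisson: Φ(2.84 - 2.38) = .68.

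**The case against.** The strongest reply is that the protocol never says the errors are model-based. Poisson regression with robust errors is still Poisson regression, so the remedy fits the text as written, and the choice of variance estimator may sit in a SAP that is not at hand. This stands in part: a reader might infer that the protocol prescribes the wrong variance, and it does not. What remains is that unqualified Poisson regression ordinarily means model-based errors, and the protocol pairs it with a binary measure without saying that anything more is needed.

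Three other strong inferences also go too far.
- *That a real STI effect is likely to be missed.* At the protocol's own 20% vs 38%, power stays above .99 either way. The drop from .81 to .68 needs an intervention risk of 28.25%, which appears nowhere in the protocol.
- *That 16% applies throughout.* It applies to the overall STI composite at one pair of rates, and section 7's densities point to much lower six-month risks. The protocol tests each infection separately; single-infection risks cannot exceed the combined risk, so the excess is generally smaller.
- *That the trial could claim a false effect through this choice.* The error runs the other way.

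Clustering does not rescue the test. The random effect for CBO is described for the behavioral model and is not repeated in the STI sentences. If the intervention effect varies between CBOs, ignoring that would understate the standard error, but an overstated binomial variance is no substitute for modelling it.

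**Conclusion.** The concern holds in a limited form. Read in its ordinary sense, the plan tests a binary outcome with a variance that is too large. The standard error of the log risk ratio is overstated by about 16% for overall STI at 20% vs 38% (15% to 18% if the 40% reduction is taken literally), by about 5% at roughly 7% vs 12%, and by about 0.5% for HIV. True type I error falls below 5%, to about 2% at a common risk of 29%. The cost is wider intervals and some power for effects smaller than 20% vs 38%.

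This rests on three assumptions: that Poisson regression is meant for cumulative incidence as well as density, that errors are model-based, and that women are independent. If robust errors are intended, the problem disappears and only the wording needs completing. The change is worth making but does not threaten the trial's validity.

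**What to change.** In section 8, Aims 3 & 4, separate the two measures.
- **Cumulative incidence:** Poisson regression with robust (sandwich) standard errors, or a binomial or log-binomial model. Report the risk ratio and the risk difference with confidence intervals; the NNT is the reciprocal of the risk difference and needs its interval.
- **Incidence density:** keep Poisson regression with a person-time offset.
- **CBO:** account for it in the same model. Sandwich errors that treat women as independent do not address clustering. If they are clustered by CBO, use a small-sample correction, since there are only 12 sites.

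The cost is a clause or two of text, with no extra data or participants. There are two small drawbacks: log-binomial models can fail to converge, so robust Poisson should be named as the fallback, and the CBO adjustment must be chosen with the small number of sites in mind.

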2b) Personal dispositional innovativeness will mediate the relationship between staff demographics and attitudes toward EBI. Specifically, staff demographics (i.e., higher education level, shorter job tenure) will be associated with higher personal dispositional innovativeness, and personal dispositional innovativeness will be positively associated with attitudes toward EBI.

2c) Social networks indicating more connectivity and positive information regarding *Mujer Segura* will be positively associated with attitudes toward EBI.

2d) Attitudes toward EBI will meditate the relationship between personal dispositional innovativeness and implementation fidelity. Specifically, personal dispositional innovativeness will be positively associated with attitudes toward EBI, and attitudes toward EBI will be positively associated with implementation fidelity.

2e) More positive attitudes toward EBI will be associated with greater implementation fidelity.

2f) Greater fidelity will be associated with more positive FSW outcomes.

Aim 3: To determine whether the implementation of *Mujer Segura* by each CBO is associated with decreased sexual risk behaviors among Mexican FSWs over a six-month period (e.g., increased condom use with clients, reductions in STI incidence);

Hypothesis 3. As in the completed efficacy study, FSWs randomly assigned to the theory-based *Mujer Segura* intervention condition will show greater reductions in high risk sexual behavior with clients (i.e., fewer unprotected vaginal and anal sex acts, lower global STI incidence) at six-month follow-up as compared to FSWs who receive standard counseling.

Aim 4: To determine whether improvements in FSWs’ sexual risk behaviors are associated with variations in intervention fidelity and counselor competency.

Hypothesis 4. Among FSWs in the *Mujer Segura* condition, improvements in sexual behavior with clients at six-month follow-up (i.e., frequency of unprotected vaginal and anal sex, STI incidence) will be associated with higher levels of counselor competency and fidelity to the implementation model.

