7. PROGRESS REPORT/PRELIMINARY STUDIES

***Mujer Segura Intervention Trial Results***

Results of the first phase of *Mujer Segura* (NIH R01 MH065849, Project #051182) were described in the following article (see Appendix 1):

[name], T.L., Mausbach, B.T., Lozada, R., [name], H., [name], S.J., Fraga, M., Orozovich, P., Abramovitz, D., de la Torre, A., Amaro, H., Martinez, G., Magis-Rodríguez, C., and [name], S.A. Efficacy of a brief behavioral intervention to promote condom use among female sex workers in two Mexican-u.s. border cities. *American Journal of Public Health.* 98 (11): 2051-7, 2008.

After participating in our 35-minute theory-based intervention, FSWs randomized into *Mujer Segura* had a 40% decline in cumulative STI incidence (p=0.03). Incidence density for the intervention vs. control was 13.8 vs. 24.92 per 100 person-years (py) for STIs combined (p=0.03), and 0 vs. 2.01 per 100 py for HIV (p<0.001), with concomitant increases in total numbers and percentages of protected sex acts and decreases in total numbers of unprotected sex acts with clients (p<0.05) at six-month follow-up. These results establish a baseline for efficacy against which successive implementations of *Mujer Segura* at other sites within Mexico can be measured.

Our human-subjects experience with *Mujer Segura* was excellent. A total of 1,853 participants were recruited, and none complained about any aspect of her treatment. Participant confidentiality was effectively maintained throughout the study. This was due to thorough training of staff at all implementation sites on the importance of informed consent and participant confidentiality. The same training measures will be implemented in the present study at all implementation sites.

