***Intervention Study Participants (FSWs)***

The second set of participants in this research will be the FSWs who are recruited at each CBO to participate in the baseline and follow-up assessments and either the *Mujer Segura* counseling intervention or the “usual care” comparison condition. The recruitment goal for the study will be 960 female sex workers (FSWs) from the twelve anticipated sites (12 CBOs times 80 FSWs per site = 960). As with the staff participants (see above), we are uncertain whether the all of the currently projected sites will be able to meet this quota. We also face the uncertainty (particularly in the early phases of the study) whether, once the study has been started at a particular site, the staff will be able to carry it to completion due to factors beyond our or Mexfam’s control. Accordingly, we request flexibility in the per-clinic and overall figures for recruiting FSWs, up to a maximum of 1,090 for the entire study (in increase of 130, which is 13.5% more, or the equivalent of less than two additional sites).

We anticipate that participants will range in age from 18 to 50 years (mean approx. 33); mean level of educational attainment will be 6 years; 80% will be married or living in a common-law relationship; and 94% will have children.

Inclusion Criteria: To be eligible for this intervention, participants must be:

1) Biologically female,

2) At least 18 years old,

3) Report having exchanged sex for money, goods or drugs within the previous 30 days,

4) Report having unprotected vaginal or anal sex with a male client at least once during the previous month.

Exclusion Criteria:

1) Consistent use of condoms for vaginal and anal sex with all male clients during the previous month,

2) Known to be HIV+ or test HIV+ for the first time on-site at MexFam clinic,

3) Being under 18 years of age,

4) Being male or transgendered,

5) Being incapable of giving informed consent,

Because this study is designed to transport an established, efficacious intervention into a community-based setting, we must adhere to core elements of the established intervention, which was designed for women who are biologically female. In the original intervention design, transgendered persons were excluded because this subpopulation of FSWs would require different recruitment strategies and a targeted intervention to reflect unique sexual risk behaviors and sexual milieu.

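### Poisson regression is a poor choice for testing HIV, where the protocol's own rates project about 3.9 versus 0 infections, and the Aim 3 analysis never names the combined STI outcome that was hypothesised and powered

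*Protocol*

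**What the plan says.** The analysis text for Aims 3 and 4 (Protocol section 8, Data Analysis and Interpretation) compares the groups on cumulative incidence and incidence density of HIV and other STIs. For both measures, "the numerator will be the number of women who acquire the STI in question during follow-up". The significance test is then fixed: "For each HIV/STI outcome, Poisson regression will be used to determine if group differences are statistically significant". No small-count method is mentioned, and no combined STI outcome is named in that text.

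Other sections bear on this:

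- Hypothesis 3 (section 5) predicts "lower global STI incidence" in the intervention group. HIV is not named in it.
- Section 12 counts lower incidence of both HIV and STIs among the desired primary outcomes of the study in sex workers.
- Section 7 reports the parent trial's HIV incidence as "0 vs. 2.01 per 100 py for HIV (p<0.001") and gives the combined STI result separately: "Incidence density for the intervention vs. control was 13.8 vs. 24.92 per 100 person-years (py) for STIs combined (p=0.03").
- The power statement for Hypotheses 3 and 4 (section 8) says "we will have 384 subjects per group for a total of 768 subjects at the end of five years". Its STI power of .81 refers to overall STI incidence. No HIV power is given.

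**The concern.** There are two problems, and both lie in what the protocol states.

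**HIV.** The named method does not settle the result for the data that the protocol's own rates project. With an empty arm, two analysts who both follow the text could report opposite conclusions, depending on which output of the Poisson model they read. A non-significant result, set against the parent trial's p<0.001, could also be misread as a lost HIV benefit when the trial had little chance of showing one.

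**STIs.** The hypothesis and the power calculation rest on one combined outcome, while the analysis is written infection by infection. It is unclear which result answers Hypothesis 3 and whether an incident HIV infection counts towards it.

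**Working it through.** **Inputs.** HIV incidence is 2.01 (control) and 0 (intervention) per 100 person-years (section 7). Recruitment is "12 CBOs times 80 FSWs per site = 960" (section 9). Attrition is 20% (section 8). Follow-up is six months, or 0.5 years per woman (section 8). HIV-positive women are excluded at entry (section 9), so all enrolled women are at risk.

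**The plan's own figures.** 960 × 0.80 = 768, or 384 per group, which reproduces. The STI power of .81 does not: 38% versus 20% at 384 per group gives power above .999. Using the section 7 densities over half a year (12.5% versus 6.9%), two-sided power is about .74. That mismatch is a separate matter, noted only because no power figure here can be taken as covering HIV or a single infection.

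**Expected HIV events.**

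- Person-years per arm: 384 × 0.5 = 192.
- Control: 192 × 2.01/100 = 3.86. Intervention at the parent rate: 0.
- With no attrition (480 per arm): 240 × 2.01/100 = 4.82 versus 0.

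**Tests at 4 versus 0, equal person-time.**

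| Test | Calculation | p |
|---|---|---|
| Wald | log rate ratio about −21, SE about 13,000 (not converging) | about .999 |
| Exact conditional | 2 × 0.5^4 | .125 |
| Score | (4 − 0)²/(4 + 0) = 4.00 on 1 df | .046 |
| Likelihood ratio | 2 × 4 × ln 2 = 5.55 on 1 df | .019 |

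The likelihood-ratio test is too liberal here. With both arms at 2.01 per 100 person-years, its true type I error is about .08.

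**What the exact test can show.** For k versus 0, p = 2 × 0.5^k: 5 gives .0625 and 6 gives .031, so at least 6 versus 0 is needed. P(Poisson(3.86) ≥ 6) = .19. With no attrition, P(Poisson(4.82) ≥ 6) = .35. If the true rate ratio is 0.5, exact power is about .04 and likelihood-ratio power about .18.

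**What the data could say.** At 4 versus 0 the exact 95% upper limit for the intervention share of events is 1 − 0.025^(1/4) = .602. The upper limit for the rate ratio is therefore .602/.398 = 1.5. The interval from 0 to 1.5 covers both complete prevention and no effect.

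**Combined versus single infections (illustration).** Assume that the six-month combined incidence (12.5% versus 6.9%) splits in proportion to the section 6 prevalences (gonorrhea 6.4%, Chlamydia 13%, syphilis 14.2%), with no overlap. Two-sided power is then about .19, .35 and .38, against .74 combined. Splitting 38% versus 20% in the same way gives about .55, .87 and .90, against above .999. On either basis, the combined and single-infection analyses are different tests with different power.

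**The case against.** **Poisson regression does not fail outright.** A reader might infer that the model cannot be used for HIV at all. The text does not specify a Wald test, and the likelihood-ratio and score tests remain computable at 4 versus 0. What stands is that these tests disagree across the .05 line and the text does not choose among them.

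**An empty arm is a projection.** A reader might take zero intervention events as the most likely outcome. That treats the parent trial's observed zero as the true rate. If the HIV rate ratio equalled the combined STI ratio (13.8/24.92 = .55), about 3.86 × .55 = 2.1 intervention events would be expected, and the chance of none is exp(−2.1), about .12. The model would then be estimable, but still with very little power.

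**A combined outcome is not excluded.** A reader might infer that the global STI outcome goes untested. The phrase covering each HIV/STI outcome could include a combined one, and section 7 shows that the parent trial reported one. This is an unclear definition, not a proven contradiction.

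**Multiplicity.** Four independent tests at .05 would give 1 − .95^4 = .185. The protocol sets no alpha for the incidence tests and does not say that each infection is tested twice. Infections that share an exposure are also unlikely to be independent. That figure is not relied on.

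**Matters for an analysis plan.** Small-count methods and outcome hierarchy are often left to the SAP, which is not shown. But this protocol itself fixes the test, the numerator, the hypothesis and the power basis, so their fit can be judged. It is also fair to say that HIV is absent from Hypothesis 3, and that section 8 says the study is not designed to replicate the parent findings. Section 12 nevertheless lists HIV incidence among the desired primary outcomes.

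**Conclusion.** The point holds as a recommended correction. At the protocol's own rates the HIV comparison would rest on about 3.9 control infections, or 4.8 with no attrition. If the intervention arm has none, the stated method gives no finite log rate ratio and a p-value anywhere from .019 to about .999, depending on the test read. If the arm has a few, the model can be fitted but is nearly uninformative. Exact power is about .19 at best with 384 per group, and about .04 at a rate ratio of 0.5. These figures assume that the parent control rate carries over to the new cities, full six-month follow-up for 384 women per group, and no allowance for clustering within organisations.

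On STIs, the hypothesis and the power statement refer to a combined outcome that the analysis text neither names nor defines. Whether HIV belongs in it is open. The documents do not support saying that Poisson regression is unusable or that the global outcome will not be tested.

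**What to change.** In the Aims 3 and 4 analysis text of section 8:

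1. For HIV, replace Poisson regression with counts and rates by arm and an exact conditional Poisson test and confidence interval. State that the trial is not powered for HIV, so a non-significant result is not evidence that the benefit was lost.
2. Name and define the combined STI outcome of Hypothesis 3, listing the infections and saying whether HIV counts. Make it the main biological test, by Poisson regression as planned, and label the infection-specific results as secondary.

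The cost is wording only, with no change to data collection or sample size. The exact HIV test is conservative, and infection-specific results will carry less weight. Testing the single infections as secondary outcomes remains open to the investigators.

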To avoid contamination between the experimental and comparison conditions, CBO staff will first evaluate and deliver the “usual care” counseling session to the control group before learning how to deliver the experimental counseling intervention. A total of 80 FSWs will be recruited at each site, of whom 40 will be randomly assigned to the *Mujer Segura* counseling condition and 40 will be assigned to the usual care risk-reduction counseling condition, which was developed by Mexico’s federal HIV-AIDS agency (CENSIDA) and focuses upon basic educational information, personal risk assessment, and strategies for reducing personal risk. Participants who are randomized at intake to the experimental condition will be asked to return at a later date to receive their assessment and intervention.

Phase Two: Training the CBO’s designated “internal trainer.” Once the comparison condition FSWs have been assessed and counseled, a participating CBO staff member will be designated as the CBO’s “internal trainer” and receive intensive training in both the *Mujer Segura* protocol and in effective methods for teaching the protocol to other staff. Drs. [name], [name], and [name] and two practice experts from the Ciudad Juarez training center will conduct an intensive, eight-day training.

Phase Three: The “internal trainer” trains CBO staff who in turn deliver the *Mujer Segura* intervention. The practice experts will remain at the CBO for two weeks to observe and coach the internal trainer as she trains the counselors who will deliver *Mujer Segura* to the 40 randomized FSWs, and the counselors will begin to deliver the intervention. The experts will give feedback on the delivery and help the CBO counselors resolve challenging or idiosyncratic case issues or presentations. After the practice experts leave, they will maintain weekly telephone and email contact with the CBO counselors.

While the CBO is implementing *Mujer Segura* (over approximately a six-month period), the ethnographers will return periodically to monitor intervention fidelity. Finally, at the end of implementation, the ethnographers will return to repeat the staff qualitative interviews and focus groups that were performed at the outset, in order to enable the researchers to see if any changes have occurred in staff attitudes or organizational characteristics over the course of implementing the intervention.

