16. RISK/BENEFIT RATIO

We judge the importance of the knowledge to be gained from this study to be quite high. First, we expect to significantly increase scientific knowledge of the barriers and facilitating factors associated with implementation of an efficacious behavioral intervention in a high-risk population. Second, implementation of *Mujer Segura* in 12 Mexican cities has the potential for significantly reducing the number of new HIV infections and STIs among FSWs and their clients. This is true both for the participants in the active control condition and for the recipients of the *Mujer Segura* intervention, since in the original *Mujer Segura* study, participants in the active control condition also experienced decreased in frequency of unprotected sex (see [name] et al., Appendix 1), but due to the absence of a third, “passive” or untreated control arm, it was not possible to determine whether the incidence of HIV or STIs in the active control group declined relative to an untreated group. In view of the minimal risks and the fact that even control group participants are likely to benefit, we hold that the potential benefits predominate.

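### The .78 power for unprotected sex sets control-arm change to zero, although Section 16 says the parent trial's active control improved; unless the 36% is already net of that improvement, the power is overstated

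*Protocol*

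**What the plan says.** The power paragraph for Aims 3 & 4 (Protocol Section 8, Data Analysis and Interpretation) takes its effect sizes from the parent trial. For the behavioral outcome it says "We observed a 36% reduction in unprotected sex in the intervention (i.e., 18% vs. 36", where the bracket closes on a percentage. The inputs are listed as "N=384 per group, alpha = .05, and a 36% reduction in mean number of unprotected sex acts". The scenario is then spelled out: "If subjects in our experimental condition reduced the number of unprotected sex acts while the control condition did not change". This is labeled as the group-by-time interaction, and the stated power is above 78%. The paragraph ends by calling the power sufficient.

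The analysis paragraph just before it makes intervention, time and their interaction the primary terms of the mixed model.

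Section 16 (Risk/Benefit Ratio) reports on the parent trial that "participants in the active control condition also experienced decreased in frequency of unprotected sex". It uses this to argue that women in the comparison arm of the present trial will probably gain as well.

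**The concern.** The interaction measures how much more one arm changes than the other. If the 36% is the fall within the intervention arm, it equals the between-arm effect only when the control arm stays flat. The protocol says that the parent trial's control arm did not stay flat, and it relies on that fact when justifying the trial. So control improvement counts in the risk/benefit argument and is set to zero in the power argument, with the same trial as the source for both.

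A stated power of .78 leaves little room. Even a modest control improvement would take the behavioral half of Hypothesis 3 well below that level, and the claim of adequate power would not be supported.

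The bracketed figures add a second problem: a reader cannot tell from them what contrast the 36% describes.

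**Working it through.** **Inputs**
- Sample size: "12 CBOs times 80 FSWs per site = 960" (Section 9). Allocation is 40 and 40 per site (Section 8), so 480 per arm. With 20% attrition, 480 × 0.80 = 384, which agrees with "we will have 384 subjects per group for a total of 768 subjects at the end of five years".
- Alpha .05. Sidedness is stated for Aim 2 (two-tailed) but not for Aim 3. I take two-sided and show one-sided as well.
- Effect: 36% reduction in the experimental arm, 0% in control.
- Not given: baseline mean, standard deviation, pre-post correlation, and the size of the parent control arm's reduction.

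**Can the .78 be reproduced?** Not directly, because there is no standard deviation. Reading the bracket as two proportions does not produce it: with .18 and .36 and 384 per arm, the standard error is √[(.18×.82 + .36×.64)/384] = .0314, the ratio is .18/.0314 = 5.7, and power exceeds .999. The outcome powered is a mean count, so this shows only that the bracket was not the input to the .78. It does not show that .78 is wrong. As proportions the bracket is also a 1 − 18/36 = 50% reduction, not 36%.

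**Calibration.** I therefore take the protocol's .78 as correct for its own scenario and solve for the standardized effect it implies:
- Two-sided noncentrality: 1.960 + 0.772 = 2.732.
- d = 2.732 × √(2/384) = 0.197 (0.174 one-sided).
- If 36% of the baseline mean is the full between-arm difference, the implied standard deviation is 0.36/0.197 ≈ 1.83 times the baseline mean.

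**Effect of a control-arm reduction c.** On the mean scale the remaining fraction of the effect is f = (36 − c)/36, and two-sided power is approximately Φ(2.732 f − 1.960). On the log scale f = ln[(1 − c)/0.64] / ln(1/0.64). The sample size per arm that restores .78 is 384/f² (mean scale). The values of c are assumptions, since the protocol gives a direction only.

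| Control falls by | f (mean scale) | Power, two-sided | Power, one-sided | Power, log scale, two-sided | n per arm to restore .78 |
|---|---|---|---|---|---|
| 0% | 1.00 | .78 | .78 | .78 | 384 |
| 5% | .861 | .65 | .67 | .68 | 518 |
| 10% | .722 | .51 | .54 | .55 | 737 |
| 18% | .500 | .28 | .33 | .33 | 1,536 |

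Example, c = 10%: f = 26/36 = .722; 2.732 × .722 = 1.973; 1.973 − 1.960 = .013; Φ(.013) ≈ .51.

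**The case against.** The strongest reply is that the 36% may already be a between-arm contrast. The same sentence pairs it with an STI figure expressed relative to control, and both brackets have the same form. If so, a static control is just a convenient way of writing the interaction, and the .78 stands. This cannot be ruled out. The wording leans the other way, though: the behavioral reduction is placed in the intervention arm, only the STI figure is tied to the control, and the calculation then sets a changing experimental arm against an unchanging one. If the figure is net, the text needs to say so.

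A reader might infer that the bracket shows an 18% fall in control and a 36% fall in the intervention, so that power is really .28 to .33. The documents do not support that as a finding. In the parallel STI bracket (20% vs. 38%) the lower incidence has to be the intervention, so the order there is intervention first. With that order and a reading as declines, control would have improved more than the intervention, against the parent results in Section 7. The STI bracket does not match its own headline either (1 − 20/38 = 47%, against a stated 40%), so neither bracket can carry much weight. The 18% row is one assumed point in a range.

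A reader might also add regression to the mean, since women are enrolled for recent unprotected sex. It is expected in both randomized arms and largely cancels in the interaction, so it adds no independent support.

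Two further points stand in part. The zero-change premise is stated openly as a conditional, but the power claim relies on it. The two comparison conditions are not shown to be identical (a didactic session in the parent trial, the federal agency's usual-care counseling here), but Section 16 itself carries the parent result over to this trial.

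**Conclusion.** The point holds conditionally. The zero-change premise behind the .78 conflicts with Section 16. If the 36% is a within-arm reduction, as the wording suggests, the power for unprotected sex acts is overstated; if it is already net of control change, the .78 is unaffected by this point.

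The direction under the within-arm reading is certain. The size is not: two-sided power of about .65, .51 or .28 for assumed control reductions of 5%, 10% or 18% is a sensitivity range. It is anchored to the protocol's own .78, because the control change and the standard deviation are not given.

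Separately, and on any reading as proportions, the bracket does not equal a 36% reduction.

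A reader might conclude that Hypothesis 3 as a whole is underpowered. That goes too far: the STI power of .81 rests on a contrast with control and is not touched by this point.

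**What to change.** In the power paragraph for Aims 3 & 4:

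- Recompute power for the behavioral outcome of Hypothesis 3 from the parent trial's between-arm difference in change.
- State each arm's change, the standard deviation used and whether the test is one- or two-sided.
- Say explicitly whether the 36% is net of control, and replace the bracket with a single defined contrast that yields the percentage quoted.
- Reconcile the zero-change premise with Section 16.
- Restate either the power or the smallest net reduction detectable with 384 per group, and adjust the adequacy claim to match.

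The cost is text only: no change to design, endpoint or analysis. The inputs are parent-trial results that the team should hold. If the 36% proves to be within-arm, the stated power becomes less favorable.
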